## **1. Summary**

One of the most serious challenges facing antiretroviral therapy (ART) programs for HIV/AIDS in resource-constrained settings is the failure of ART-eligible patients to complete the steps required to initiate treatment. The high rate of loss to care of patients who are treatment-eligible at HIV diagnosis may be due in part to the large number of steps required between receiving an HIV diagnosis and obtaining the first dose of antiretrovirals (ARVs). In South Africa, these steps usually require approximately four clinic visits over a period of 2-8 weeks before a patient can start treatment. One strategy proposed for reducing losses among those eligible for ART is to simplify and condense the steps required for starting treatment. This is now possible because new, point-of-care (POC) tests for CD4 counts and TB diagnosis are available. These technologies can be combined with changes to clinic schedules to allow all steps required for ART initiation under South African guidelines (lab tests, physical exam, education) to take place on the day the patient presents for an HIV test.

This study is a randomized strategy evaluation of the feasibility, effectiveness, and cost-effectiveness of rapid ART initiation. Outpatient, non-pregnant, HIV-positive adults who come to a South African clinic for an HIV test, consent to study participation, and are eligible for ART will be randomized 1:1 to rapid ART initiation or to standard care. Those who are assigned to rapid ART initiation will have the possibility of receiving their first dose of ARVs as early as the same day, while those who are assigned to standard care will follow the clinic's usual procedures for starting ART. Rapid ART initiation for HIV-positive pregnant women, which has recently become the standard of care in South Africa, will also be assessed in a programmatic evaluation conducted alongside the randomized evaluation, with a retrospective comparison group. The primary study outcome for non-pregnant adults will be remaining alive, in care and virally suppressed 10 months after having a positive HIV test or CD4 count at the study site. The primary study outcome for pregnant women will be adherence to ART until delivery. The cost effectiveness of the rapid initiation strategy will be assessed as the cost per patient achieving the primary outcome for each population.

### **3. Background**

#### 3a. Loss to HIV treatment initiation

In recent years, multiple studies have demonstrated that antiretroviral therapy (ART) for HIV/AIDS is more effective when initiated earlier in disease progression. Earlier treatment has been shown to reduce morbidity and mortality in the patient, protect the patient's uninfected partners, and potentially reduce overall medical care costs. For treatment-eligible pregnant women who learn they have HIV during the antenatal period, earlier initiation of ART significantly reduces the risks of mother-to-child-transmission.

For HIV care and treatment providers in high-prevalence settings, this research has underscored the urgent need to identify strategies that will achieve earlier treatment initiation among those already diagnosed. A recently published review of the literature on pre-ART retention in care found that roughly one third of adult patients in sub-Saharan Africa who had already been determined eligible for ART did not start ART within the studies' follow-up periods. If those diagnosed with HIV but not assessed for treatment eligibility had been added, this proportion would have been far higher. The result is persistently late initiation of treatment, even for those already accessing healthcare.

This problem is particularly apparent in South Africa, the country with the largest burden of HIV in the world. Despite aggressive HIV testing campaigns and the availability of ART in most districts, median starting CD4 counts remain well below treatment eligibility thresholds. Nationally, the average median starting CD4 count in studies published between 2007 and 2009 was 95 cells/mm^3 (IQR 72-114). In 7 studies from South Africa included in the review of pre-ART retention in care mentioned above, a median of 32% (range 16-61%) of patients who were ART-eligible under the more stringent eligibility guidelines previously in place in South Africa (CD4  $\leq$  200 for all adults) did not initiate

treatment within the period of study observation (3-12 months after confirmation of eligibility). In studies we conducted at a large public treatment facility in Johannesburg, we found that:

- More than half (54%) of those who seek HIV testing at the outpatient clinic are already treatment-eligible;
- Nearly half of those who are eligible for ART (49%) do not return to obtain their CD4 count results within 3 months, and are thus not aware of their need for treatment; and
- Even among those who do receive their CD4 count results and are eligible or fast-tracked for ART (CD4  $\leq$  250) fewer than half (46%) initiate ART within four months of HIV testing.

This problem is likely to be even worse among patients who obtain an HIV test from a mobile or stand-alone HIV counseling and testing site, and thus must be referred elsewhere for a CD4 count and other services. South Africa's recent raising of the treatment eligibility threshold to CD4  $\leq$  350 is likely to exacerbate this problem further, as more asymptomatic patients become eligible.

Failure to initiate ART promptly is also an acute problem amongst pregnant women who are diagnosed with HIV during antenatal care. A study in Cape Town, South Africa found that only half (51%) of pregnant women who were eligible for full HAART (three drug treatment regimen rather than PMTCT regimen) under previous guidelines (CD4 count  $< 200$  cells/mm^3) initiated treatment prior to delivery, increasing the risk both to themselves and to their infants.

### 3b. Reasons for high rate of loss

Although studies in different parts of Africa have identified several psycho-social and structural reasons for failing to start ART, one major barrier is clearly the daunting number of steps required between receiving an HIV diagnosis and obtaining the first dose of ARVs. In South Africa, these steps include:

- 1) Confirmation of treatment eligibility (CD4 count);
- 2) TB diagnosis and treatment initiation if indicated;
- 3) Hemoglobin, liver function, pregnancy, and creatinine clearance tests;
- 4) General medical exam; and
- 5) Several (typically 3-4) wellness/treatment readiness/adherence sessions.

Except for the sickest patients, these activities usually require several clinic visits and a 1-2 month interval to complete even if patients adhere to the clinic's schedule. Standard laboratory technologies and procedures in use throughout sub-Saharan Africa typically require patients to make two clinic visits per diagnostic test, one to provide a sample and another to receive results. As laboratories have struggled to keep pace with the expansion of treatment programs, the time interval between these two visits has increased in many locations. In the research team's experience in South Africa, completion of a baseline CD4 count for determination of treatment eligibility can take between 2 days and 4 weeks, depending on the location of the lab, the time required to process the sample, and the promptness of the patient's return. Similarly, diagnosis of pulmonary TB requires anywhere from 2 days to 6 weeks or longer, depending on the type of TB (smear positive or smear negative), backlog at the laboratory, and delays in communicating results to the treatment site and thence the patient. Since up to 70% of HIV patients may be considered TB suspects and require TB diagnosis even though  $< 20\%$  have TB, TB diagnosis also causes substantial delays in ART initiation and leads to high loss to follow up from both HIV and TB treatment.

At the treatment site in Johannesburg where the study team is based, the average interval between the first CD4 count that indicates treatment eligibility and treatment initiation is 42 days among those who do start treatment within 16 weeks and entails an average of 4 visits to the site. Even very sick patients usually face a delay of at least 2 weeks before initiation. In addition to delay in starting treatment, each clinic visit entails time, transport costs, and possibly child care and other costs for the patient. Previous research at the same site estimated that the median cost to an ART patient per clinic visit was R29 (\$4.15) (inflated to 2011 prices) for transportation alone, the equivalent of roughly a third of a day's wage for a domestic worker. Each visit also required a median of two hours' travel time. A more recent study found that, due largely to waiting time, the average duration of a routine clinic visit for a stable ART patient at this site is just under 6 hours; even simply picking up medication, without any clinical consultation, requires nearly 3 hours. Requiring multiple visits before dispensing medications thus constitutes a major obstacle to treatment initiation, in addition to other possible reasons for loss to follow up.

### 3c. Potential solution: accelerated initiation using rapid diagnostics

One strategy proposed for reducing loss to ART initiation among those eligible is to shorten the time interval and simplify the process required for initiation, ideally allowing ARVs to be dispensed at the same visit as the HIV test or, if the patient was previously diagnosed, first visit for HIV-related care. Acceleration of the required steps is now possible under existing South African treatment guidelines due to the advent of new, rapid diagnostic tests. All the laboratory tests required for treatment initiation can now be done quickly, using the following equipment, all of which has been approved for use in South Africa:

- Assessment of CD4 count to determine ART eligibility with the Pima™ Analyzer (Alere) (<http://pimatest.com/en/pima-platform/pima-analyser.html>). The Pima assay uses a capillary bleed or venous blood sample and takes 20 minutes for results to be available once the cartridge containing sample has been inserted into the instrument.
- TB diagnosis with Xpert® MTB/RIF (Cepheid) ([http://www.cepheid.com/media/files/eu/brochures/XpertMTB\\_Broch\\_R9\\_EU.pdf](http://www.cepheid.com/media/files/eu/brochures/XpertMTB_Broch_R9_EU.pdf)). Xpert uses a sputum sample and takes approximately 1 hour and 45 minutes to complete once the cartridge containing the sample has been inserted into the instrument and 2.5 hours overall, including sample collection and delivery of results to the patient. The World Health Organization has endorsed the use of Xpert as the first-line TB diagnostic test in HIV-positive TB suspects, and South Africa has announced plans to utilize Xpert at National Health Laboratory Service laboratories nationally.
- Liver function (alanine aminotransferase) and creatinine clearance using Reflotron Plus (Roche) (<http://www.roche-diagnostics.co.in/Products/Pages/ReflotronPlusDry.aspx>).
- Hemoglobin using the HemoCue® Hemoglobin System^26 (<http://www.hemocue.com/international/Products/Hemoglobin-1155.html>).

These tests, combined with those already routinely used as point-of-care rapid tests (e.g. pregnancy), should allow full laboratory evaluation for treatment eligibility and treatment regimen selection to be completed within roughly a half-day interval. The non-laboratory steps in the initiation process can also be completed rapidly if service delivery schedules are deliberately arranged to do so. In a facility with a rapid-test equipped laboratory and willingness to manage schedules accordingly, it is thus now possible to initiate ART on the same day as the HIV test for patients who are treatment-eligible at HIV diagnosis.

Several recent studies provide some initial evidence that the use of rapid diagnostics may accelerate treatment initiation in South Africa. Figure 1 summarizes the results of four evaluations of the impact of rapid CD4 counts on uptake of care.

**Figure 1. Impact of rapid CD4 counts on uptake of care in South Africa**

[figure not shown]

Sources: Faal et al ; Larson et al ; Jani et al ; Larson et al 

An evaluation of a pilot program allowing same-day treatment initiation for eligible pregnant women in Cape Town, which incorporated Pima™ CD4 counts but did not use rapid tests for TB or other indicators, found that of 101 treatment-eligible pregnant women, 89 (88%) did initiate ART on the same day as their HIV test. Although less comprehensive than what is proposed here and observational in design, these preliminary studies suggest that rapid diagnostics are acceptable to patients and facilitate uptake of treatment.

Same-day treatment initiation could increase treatment uptake, improve patient outcomes, and save resources for both the patient and provider. It also raises a number of implementation questions, however, including:

- Will patients accept rapid treatment initiation?
- Will the availability of rapid initiation reduce losses to care prior to starting ART?
- Will rapid initiation improve overall treatment outcomes, or will an increase in early attrition after starting ART offset the gains in the pre-ART period?
- Will the feasibility and uptake of rapid initiation be the same for pregnant women as for non-pregnant adults?
- Will rapid initiation be affordable and cost-effective compared to standard care, taking into account the costs of all medical care provided before and after starting treatment?

Some patients who are offered rapid ART will likely agree to start treatment immediately even if for social, psychological, economic, or other reasons they are not personally ready. Under standard care these patients might not have started treatment at all, or started later. Under rapid initiation, they may instead accept the first month or two of medications but then drop out. It is therefore important to evaluate not only the immediate acceptability and feasibility of rapid ART initiation, but also whether it can generate equally good medical outcomes, as indicated by viral suppression, which is the basic goal of antiretroviral therapy.

#### **4. Objectives**

##### 4a. Primary objectives

The primary objectives of this study are to:

1. For non-pregnant adults, compare the proportion of ART-eligible patients who are alive, in care, and virally suppressed within 10 months of having an HIV test or enrolling in HIV care between ART-eligible patients offered rapid ART initiation or standard ART initiation
2. For pregnant women, estimate the proportion of HIV-positive patients who adhere to ART until delivery, as indicated by monthly medication pickup.

##### 4b. Secondary objectives

1. For non-pregnant adults, compare the cost per patient alive, in care, and virally suppressed within 10 months of an HIV test or enrollment in HIV care for those offered rapid ART initiation to the cost for those offered standard care.
2. For pregnant women, estimate the cost per patient adhering to ART through delivery and the cost per infant infection avoided, using estimated vertical transmission rates.
3. Estimate the proportion of patients alive, on ART, and virally suppressed at 6 month intervals after treatment initiation and at the final date of data censoring.
4. Estimate the average time interval between HIV test or first HIV or ANC care visit and treatment or PMTCT initiation before and after rapid ART initiation became the guideline procedure for pregnant women.
5. If enrollment numbers allow, among pregnant women, stratify the primary outcome (the proportions of subjects achieving retention on ART or PMTCT regimen until delivery) by CD4 count > 350 and  $\leq 350$ .
6. Compare the average gestational age at ART initiation and average number of weeks on ART prior to delivery for pregnant women before and after rapid ART initiation became available.
7. Identify patient-level predictors of treatment uptake, retention in care, and viral suppression.
8. Describe the prevalence of TB symptoms and confirmed TB, time to initiation of TB treatment, and time to initiation of ART among patients with TB.
9. Evaluate the feasibility of the rapid initiation strategy in terms of patient acceptance, actual time between HIV test/enrollment in care and dispensing of first dose of ARVs, and patient costs incurred.

#### **5. Study Design**

##### 5a. Overview of study design

The study will be divided into two tracks, based on the study populations to be included.

Track 1: *Non-pregnant adults*. Track 1 will be a randomized comparison of rapid initiation of ART to the current standard of care for non-pregnant, treatment eligible adults. Patients testing positive, providing a blood sample for a CD4 count, or receiving a CD4 count result will be individually randomized 1:1 to either the rapid ART initiation strategy (rapid group) or the standard ART initiation strategy (standard group). Patients in the rapid group who are found to be eligible for ART will be offered the opportunity to initiate ART in the fastest time feasible given individual circumstances, and whenever possible on the same day as study enrollment. Patients in the standard group will be offered standard treatment initiation as currently implemented by the study site.

Track 2: *Pregnant women*. Track 2 will be a programmatic evaluation of rapid initiation of ART for pregnant women. Immediate ART initiation on the day of a woman's first antenatal care visit was introduced in South Africa in a guideline revision in April 2013 and is now the standard of care at the study site. Guidelines call for women to remain on ART for the duration of pregnancy regardless of their initial CD4 count. Adherence to ART during pregnancy, as measured by monthly medication pickups, will be compared to adherence before rapid initiation was offered.

In Track 1, those in the rapid initiation group will be offered a rapid CD4 count, rapid TB test if needed, and other rapid tests and same-day physical exam, counseling, and adherence education on the same day as study enrollment, allowing immediate ART initiation if eligible. Those in the standard group will follow the standard-of-care visit schedule and procedures, which also include a CD4 count, TB test if needed, other tests, physical exam, counseling, and adherence education, though not on a rapid schedule. Subjects in Track 1 will be prospectively followed for a minimum of 10 months. Follow-up (after treatment initiation) will be passive and by medical record review only, to prevent biasing outcomes through active follow-up and maximize the extent to which study results reflect what could be expected in a routine implementation setting. An additional retrospective comparison group for Track 1 will be enrolled comprised of patients who became eligible for ART at one of the two study sites prior to the launch of the study.

Track 2 will be an observational evaluation only. Data from before the guideline change will be collected retrospectively, from existing registers and records at the site. Data from after the guideline change will be collected prospectively from questionnaires and newly-acrued medical record data. The study will not provide any direct clinical interventions for Track 2.

Unit cost data will be collected for all resources used for patient care for both study tracks, including all drugs, diagnostics, clinical staff time, and infrastructure and other fixed costs. Quantities of resources used will be collected from study case report forms at the end of the follow up period. An average cost per patient and cost per outcome will then be calculated and compared between the strategies.

#### 5b. Study site

The study will be conducted at:

1. Thuthukani Primary Health Clinic, Ivory Park, South Africa. Thuthukani is public-sector primary care clinic and HIV comprehensive care management and treatment (CCMT) site under the authority of the

City of Johannesburg and the Gauteng Province Department of Health. It is located in a densely-populated, under-served community in the area between Johannesburg and Pretoria known as Midrand. Thuthukani maintains a large antenatal care clinic with prevention of mother-to-child transmission (PMTCT) services and provides TB treatment and other primary care.

By July 2012, Thuthukani had started almost 7000 adult patients on ART. It currently initiates roughly 840 non-pregnant adult patients and 120 pregnant women onto ART annually. Thuthukani was selected as an appropriate site for this study due to the availability of general outpatient HIV testing, HIV testing for pregnant women, TB treatment, and ART in a single facility, allowing rapid initiation for both study populations at a single site. It is a primary health clinic located in a densely-populated, under-served, township setting typical of urban sub-Saharan Africa, and study results should thus be generalizable to other areas of South Africa and the region.

2. Themba Lethu Clinic, Helen Joseph Hospital, Johannesburg. Themba Lethu Clinic (TLC) is a public sector HIV comprehensive care management and treatment (CCMT) site located in an academic hospital under the authority of the Gauteng Province Department of Health. It serves an urban population in Johannesburg and is one of the largest HIV clinics in the country, initiating nearly 10,000 adult patients onto ART annually. It was selected as a site for Track 1 of this study due to its large patient volume, existing point-of-care laboratory infrastructure, and difference in facility characteristics from the other study site (Thuthukani). It is typical of a large hospital-based HIV clinic in South Africa.

Thuthukani Primary Health Clinic and Themba Lethu Clinic both fall under the FWA of the University of the Witwatersrand Human Ethics Review Committee (Medical). A letter confirming the local government authority's agreement for each site to participate in this study will be submitted to the BUMC IRB and Wits HREC prior to study enrollment at that site.

### 5c. Study population

The study population will be adults who test positive for HIV at the study site's walk-in HIV voluntary counseling and testing (VCT) service and adults who have previously tested positive for HIV but are providing a blood sample for a CD4 count or receiving CD4 count test results. Non-pregnant patients will be eligible for enrollment in Track 1 and pregnant patients will be eligible for enrollment in Track 2.

#### *Inclusion criteria:*

- Adult patients ( $\geq 18$  years)
- For Track 1, tested HIV-positive at study site's outpatient testing service on day of study enrollment or previously tested HIV-positive but providing a blood sample for a CD4 count or receiving CD4 count test result on day of study enrollment
- Eligible for antiretroviral therapy under prevailing South African guidelines\*

#### *Exclusion criteria:*

- Currently on ART or on ART at any time in the past 12 months (three-drug combination; previous PMTCT regimen exposure for an earlier pregnancy is not an exclusion criterion)
- Stated intention to seek further HIV care during the next 12 months or antenatal care before completion of the current pregnancy at another site, not at the study site
- Not physically or emotionally able to participate in the study, in the opinion of the investigators
- Not willing or able to provide written informed consent to participate in the study

- Previously enrolled in the same study
- Diagnosed with drug-resistant TB or on MDR-TB treatment
- For Track 1 only, pregnant (pregnancy is an exclusion criterion for Track 1 because treatment guidelines for pregnant women differ from those for non-pregnant adults)

*\*Current South African treatment eligibility criteria for non pregnant HIV-positive adults are:*

- *CD4 count  $\leq$  350; or*
- *Tuberculosis, regardless of CD4 count; or*
- *WHO Stage 4 or Stage 3 condition, regardless of CD count (hereafter “Stage 4/3”)*

*All pregnant HIV-positive women are eligible for ART.*

Subjects in Track 1 will be followed prospectively and will be asked for written informed consent prior to study enrollment. An additional Track 1 retrospective comparison group will be enrolled comprised of patients who became eligible for ART at one of the two study sites (Thuthukani Clinic) prior to the launch of the study, with data collection limited to retrospective medical record review. In Track 2, subjects offered rapid initiation by the study clinic under the new standard of care will be followed prospectively and asked for written informed consent before study enrollment. For subjects in the comparison group in Track 2, data will be collected retrospectively through medical record review only. The study team will have no contact with these subjects, and informed consent will not be sought.

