#### 6f. Retrospective comparison group

As a second comparison group for Track 1, in addition to the standard group, data will be collected retrospectively for a sample of patients who were determined to be eligible for ART at Thuthukani Clinic during the 12 month period preceding the start of Track 1 enrollment. As there were no major changes to South African treatment guidelines during this period, the retrospective comparison group will provide information about uptake of ART before any study-related changes were made at the clinic.

Eligible subjects for the comparison group will be selected from the HIV counseling and testing (HCT) register maintained by the study clinic. This register indicates patients newly found to be ART-eligible from among those receiving an HIV test or a pre-ART CD4 count. Patients who became eligible over the period April 2012-March 2013 will be enrolled consecutively, starting with the later date and working backward in time until the target sample size is reached. Follow up data on pre-ART care, ART initiation, retention on ART, and viral suppression at 6 months will then be collected from the site's ART clinic files and electronic medical record system. Each subject will be followed for a 10-month period from the date at which the clinic determined that the patient was eligible for ART, corresponding to the 10-month primary outcome indicator for Track 1. A temporary identifier linking the HCT register record to the follow-up records will be created and retained until all data pertaining to an the individual study subject have been collected and quality checked. Because all data will already exist at the time the sample is selected, the identifier will serve only to link records at the same site, and all records can be accessed on site, at the same time, the identifier for any individual subject will be kept for a very short period.

Procedures for collecting data for this group will be similar to those used for the Track 2 retrospective group, described below. The study will have no direct interaction with subjects in this group.

## 7. Procedures for Track 2

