#### 7b. Procedures—retrospective (pre) group

Subjects for the Track 2 “pre” group (pregnant women offered standard care by the site before the guideline change) will be selected from the site's PMTCT register. Subjects who meet inclusion/exclusion criteria will be enrolled consecutively up to the maximum sample size for this component of the study is reached. Data collection for these subjects will be by record review only.

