Track 2: The primary outcome for Track 2 is the proportion of subjects in each group who adhere to ART or the prior PMTCT regimen until delivery. The number of weeks a pregnant woman is on ART before delivery is the most important predictor of perinatal HIV transmission. The guideline change to immediate ART initiation for pregnant women is likely to lead to earlier initiation for most pregnant women, but the intervention will be effective only if patients adhere to ART through the duration of pregnancy. Adherence will be measured as making monthly medication pickups to allow a continuous supply of ARVs through delivery. The analysis period for the primary outcome will start on the day of study enrollment, which is the date of a positive HIV test or the first antenatal visit of the current pregnancy, for women previously diagnosed, and end at the actual or estimated delivery date.

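### The exclusion for women who say they will seek care elsewhere can be applied only to the interviewed Track 2 group, which tends to tilt the before/after adherence comparison towards the post period

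*Protocol*

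**What the plan says.** Protocol section 5c gives one list of exclusions for both tracks, and only pregnancy is marked as specific to Track 1. One entry is "Stated intention to seek further HIV care during the next 12 months or antenatal care before completion of the current pregnancy at another site" other than the study site. Two others are "Not physically or emotionally able to participate in the study, in the opinion of the investigators" and "Not willing or able to provide written informed consent to participate in the study".

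Prospective Track 2 women are referred by counselors and asked for consent (7a i). Section 8b has a screening form that records each criterion, with a separate version for each track.

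The pre group is taken from the PMTCT register. Section 7b states that "Subjects who meet inclusion/exclusion criteria will be enrolled consecutively" and that "Data collection for these subjects will be by record review only". Section 5c adds: "The study team will have no contact with these subjects, and informed consent will not be sought".

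On the outcome, section 11a i states: "Adherence will be measured as making monthly medication pickups to allow a continuous supply of ARVs through delivery". Section 7d follows women through records kept by the study site and goes to other facilities only for delivery information.

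The Track 1 retrospective group (6f) is also drawn from a register: "The study will have no direct interaction with subjects in this group".

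**The concern.** A stated intention exists only if someone asks. The prospective women are asked and the pre group is not, and the abstraction fields in section 8e contain nothing that could stand in for the answer. Section 7b therefore sets a rule that cannot be carried out for this criterion.

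The criterion is closely tied to the outcome. A woman who moves her antenatal care stops collecting medication at the study site, and that is where adherence is read. The consent addendum that opens a new clinic's records is provided for Track 1 subjects only (6e ii, 12e), so Track 2 has no stated route to pickups made elsewhere.

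Track 2 is not randomised, so like-for-like selection is its main protection. Removing likely leavers from one period can create a difference that would be read as an effect of the guideline change. The regression adjustment in section 11b uses recorded baseline covariates and cannot reach an intention that was never recorded in the pre group.

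**Working it through.** **The plan's own figure.** Section 10 sizes Track 2 for 77% against 96% (19 points), alpha 0.05, power 90%, 1:1, and gives 76 per group. Taking alpha as two-sided (not stated) and the mean rate as 0.865:

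- Uncorrected: n = [1.960·√(2·0.865·0.135) + 1.282·√(0.77·0.23 + 0.96·0.04)]² / 0.19² = (0.947 + 0.595)² / 0.0361 = 65.9.
- Continuity-corrected: (65.9/4)·[1 + √(1 + 4/(65.9·0.19))]² = 76.04.

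The stated 76 is reproduced with the correction, although the text calls the test uncorrected. That has no bearing on this point. The 19-point target is the yardstick below.

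**Which criteria can be applied to which group**

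| Criterion (5c) | Prospective group | Register-drawn pre group | Direction of bias |
|---|---|---|---|
| Stated intention to go elsewhere | Asked at screening | Cannot be known | Favours post period |
| Physical or emotional fitness | Judged at screening | Cannot be judged | Plausible, not shown |
| Consent | Required | Not sought, by design | Plausible, not shown |

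**Size of the stated-intention effect.** Inputs:

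- Pre-group adherence of 0.77, leavers included. This is section 10's figure, used here as an assumption.
- s, the share who would state an intention to leave. It is not in the documents; 2% to 10% is assumed.
- q, the proportion of those women still counted as adherent from site records. It is not in the documents; 0 and 0.5 are assumed.
- No true effect of the guideline change.

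Women who leave without having said so are in both groups and cancel out. The post group, with stated leavers removed, shows

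p_post = (0.77 − s·q)/(1 − s).

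| s | q | p_post | Spurious gap (points) |
|---|---|---|---|
| 2% | 0 | 0.77/0.98 = 0.786 | +1.6 |
| 5% | 0 | 0.77/0.95 = 0.811 | +4.1 |
| 5% | 0.5 | 0.745/0.95 = 0.784 | +1.4 |
| 10% | 0 | 0.77/0.90 = 0.856 | +8.6 |
| 10% | 0.5 | 0.72/0.90 = 0.800 | +3.0 |

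If 0.77 is instead taken as the leaver-free rate, the gap at q = 0 is 0.77·s: 1.5, 3.9 and 7.7 points at 2%, 5% and 10%. The choice of convention matters little.

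**After the change.** If the criterion is applied to neither period, stated leavers stay in both groups and this source of bias disappears. The required 76 per group does not change.

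**The case against.** The best case for the plan has four parts.

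- **The consent difference is inherent.** Comparing consented women with a record review is a declared feature of the pre/post design. Women who decline carry on with a standard clinic visit (7a i), under the same guideline of immediate treatment, and nothing shows that they collect medication less often. The same holds for women judged unfit. This stands. A reader might infer that all three exclusions inflate the difference, but the documents support a direction only for stated intention.
- **A move is not automatically a failure.** Section 8e lists transfer to another site as a status separate from loss to follow-up. Section 11a i does not say how transfers count, and a SAP may settle it. This stands too. Scoring every pre-group woman who moved as non-adherent is an inference. An undocumented move would nevertheless probably look like missed pickups.
- **The size is unknown.** The share of stated leavers is undocumented, and q = 0 is the worst case. The 77% itself is a proxy from another site (at least one visit after delivery, among women who had started ART). This limits any claim about size. It does not remove the asymmetry.
- **Track 2 is observational.** Its primary objective in section 4a is worded as estimating a proportion, and section 11b admits the lack of randomisation. However, section 5a plans the comparison with the earlier period and section 10 sizes Track 2 for it, so the comparison has to be made on groups selected alike.

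**Conclusion.** The point holds for the stated-intention exclusion. It applies to Track 2, can be ascertained only in the prospective group, and tends to bias the before/after adherence difference in favour of the post period. Adjustment for recorded covariates cannot correct this.

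The size rests on assumptions about s and q. The spurious gap runs from under 2 points when few women state an intention to leave to about 9 points at 10% with no site pickups, against a planned 19.

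A reader might go further and infer that the exclusion could account for the whole planned effect. That would need 20% stated leavers, none with site pickups (0.77/0.80 = 0.9625, a gap of 19.3 points), and the documents give no support for such a share. For the same reason, no false-positive rate can be stated as a finding.

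For unfitness and refusal, the difference between periods should be reported as a limitation of unknown direction. The randomised Track 1 comparison is unaffected, because both arms are screened alike. The Track 1 retrospective comparison has the same structure, but it is secondary.

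**What to change.** - **Section 5c:** do not apply the stated-intention exclusion to Track 2. The study gives these women no intervention and follows them only through records.
- **Section 7b:** state that the pre group is selected on criteria readable from records (age, HIV status, ART in the past 12 months, drug-resistant TB). Use the same criteria for the post group, apart from consent and fitness to participate, and report those two as a limitation.
- **Transfers:** state that documented transfers-out are treated identically in both periods.
- **Section 6f:** the exclusion stays for the randomised Track 1 arms. State that it cannot be applied to the register group, and label that comparison as subject to this selection.

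A sensitivity analysis that adds all refusing or unfit women to the post group as non-adherent is not a suitable substitute, because it builds in the opposite bias. With an assumed 10% or 20% non-participation, a true 96% becomes 0.96·0.90 = 86.4% or 0.96·0.80 = 76.8%, and the latter erases the planned difference. The pre-screening log is also anonymous and filled in before the criteria are checked, so its counts may include ineligible women. If such an analysis is shown at all, it should be labelled an extreme bound.

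The cost is protocol wording, and the sample size does not change. The downside is that some enrolled prospective women will move their care, so the observed post-period adherence rate may be lower.
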